### Implementation outcomes

An overview of the process indicators and methods of measurement for the feasibility study and process evaluation are presented in Table 1.

**Table 1 Tab1:** Overview of process indicators and methods of measurement and data collection

Domain	Method	Process indicators	Data sources
Reach and uptake	Descriptive quantitative evaluation	Number of patients referred for the intervention Number of patients included of all eligible Referral patterns	Screening data
Effectiveness	Preliminary quantitative evaluation of endpoints in Phase 2 and quantitative evaluation of endpoints in Phase 3 Cost-effectiveness analysis Cost-utility analysis	Number and length of hospital admissions Patient reported outcomes Change in caregiver burden Staff time, training, materials Healthcare utilization QALYs gained	Medical records PRO-Pall EQ-5D-5 L ZBI Danish DRG tariffs EQ-5D-5 L
Adoption		Proportion of sites offering the intervention	Information from study sites
		Differences in implementation between implementation sites	
*Implementation:* Feasibility: *The degree to which the intervention can be carried out in a given setting.*	Mixed-method evaluation Descriptive quantitative evaluation Qualitative evaluation	Resource utilisation Palliative care planning processes No. of invitation leaflets handed out to participants and families No. of palliative conversations per participant No. of informal caregivers participating in palliative conversations. No. of PRO-Pall questionnaires completed for each palliative conversation. No. of medical interventions. No. of patients referred to palliative care teams No. of patients referred to hospices No. of patients referred to municipal offers (exercise, nutrition, alcohol treatment, etc.) Patient experience Caregiver experience Healthcare personnel experience	Self-developed questionnaire with open-ended questions on experiences with palliative care, pre-study training, and the intervention
*Fidelity: The degree to which the intervention was implemented as intended.*			Informal conversations with health care professionals
Acceptability and Appropriateness: *The perception among implementation stakeholders that a given intervention is agreeable*,* palatable*,* or satisfactory.*			Semi-structured interviews informal caregivers and patients
			Medical records
			Semi-structured qualitative interviews

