Maintenance	Qualitative and quantitative evaluation	Measures on Reach, effectiveness, after 12 months, two years, three years and five years.	

The feasibility study, Phase 2, explores the acceptability and implementation of the palliative care intervention. Using a mixed-method design and the RE-AIM Framework, the study assesses reach, uptake, fidelity, and preliminary patient and caregiver outcomes across the departments.

Qualitative interviews with patients, informal caregiver, and healthcare professionals will be conducted to assess the intervention’s acceptability and appropriateness. Two subgroups of approx. 20 patients and 20 informal caregivers (five from each study center) will be interviewed to explore their experiences with the intervention. Study nurses and hepatologists involved in delivering the palliative care intervention will be interviewed to assess their perspectives on its implementation and impact as part of Phase 3, the intervention study.

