The qualitative analysis will follow a systematic approach inspired by content analysis as described by Graneheim and Lundman [44]. An initial overview of each transcript will be obtained through repeated reading. Subsequently, each patient’s experiences and interpretations will be analysed line by line to identify meaning units. Relevant meaning units will be selected, condensed, and coded to reflect the content while preserving context. Codes will be sorted into mutually exclusive categories and subcategories, comparing and describing different experiences regarding knowledge needs across disease etiology and severity [44]. NVivo software (NVivo qualitative data analysis software; QRS International Pty Ltd. Version 12, 2018) is used for the initial sorting of data. The analytical process will alternate between software-based and manual processing to facilitate data management and ensure a comprehensive overview. All categories and meaning units will be re-examined to ensure validity and consistency across the dataset.

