The inclusion of an initial feasibility study further strengthens the overall study design and reflects the MRC framework’s recommendation to assess feasibility before conducting a full evaluation of complex interventions [23]. Feasibility testing allows us to assess acceptability, fidelity, recruitment pathways, workflow, and data-collection procedures before launching the full trial [47]. These insights will guide refinements of both the intervention and implementation strategy, thereby reducing the risk of attrition, non-adherence, and site-level variation later in the study. Taken together, the feasibility phase and process evaluation increase the likelihood that the intervention will be not only effective but also implementable and scalable.

The multicenter design enhances generalisability but introduces the possibility of variability in prerequisites between sites in terms of culture, staffing, resources, and local workflows. Such heterogeneity may affect fidelity and complicate interpretation of outcome data [23]. The process evaluation is therefore crucial in documenting contextual influences and enabling nuanced understanding of how and why outcomes differ across settings. This knowledge is essential for future scale-up beyond the study sites.

The results of the LiverCare study will be disseminated in peer-reviewed journals and at national and international conferences. Findings will inform clinical practice and support education and competence development for healthcare professionals working with advanced liver disease. Insights will also guide future implementation strategies and contribute to strengthening palliative care provision within hepatology.

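### As stated, the qualitative analysis is directed at patients' knowledge needs, not at the acceptability and appropriateness that the interviews with patients, caregivers and staff are meant to assess

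*Protocol article*

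**What the plan says.** **Purpose of the interviews.** Under Implementation outcomes: "Qualitative interviews with patients, informal caregiver, and healthcare professionals will be conducted to assess the intervention’s acceptability and appropriateness". Table 1 defines acceptability and appropriateness together, starting with "The perception among implementation stakeholders that a given intervention is agreeable"; the definition refers to stakeholders, not to patients alone.

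**Who is interviewed.** The same section states: "Two subgroups of approx. 20 patients and 20 informal caregivers (five from each study center) will be interviewed". Study nurses and hepatologists "will be interviewed to assess their perspectives on its implementation and impact as part of Phase 3".

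**How the interviews are analysed.** The qualitative paragraph under Statistical methods begins with repeated reading of all transcripts. Next, "each patient’s experiences and interpretations will be analysed line by line to identify meaning units". Relevant units are selected, condensed and coded according to their content. The codes are then sorted into categories, "comparing and describing different experiences regarding knowledge needs across disease etiology and severity".

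**What the process evaluation is for.** The Discussion relies on it for "enabling nuanced understanding of how and why outcomes differ across settings".

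**The concern.** The article states a purpose for the interviews and a method for analysing them, and the two do not meet. The method names a topic that the trial does not otherwise study, one of the three groups interviewed, and two comparison axes that belong to the patient's disease. The named endpoints, the other two groups and the study site do not appear in it.

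The design is a hybrid type 1 study, so implementation is the second half of its stated dual focus, and implementation outcomes are part of the stated aim. If analysts follow the paragraph as it stands, the categories they report will answer a question about information needs, and the views of caregivers and staff will have no explicit place. If they do not follow it, the published method will misdescribe what was done, and a reader of the results will be unable to tell whether the change was planned.

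**Working it through.** No formula or stated figure is involved. The check sets the stated purpose beside the stated analysis.

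| Element | Implementation outcomes, Table 1, Discussion | Qualitative paragraph, Statistical methods |
|---|---|---|
| Topic | Acceptability and appropriateness of the intervention | Knowledge needs |
| Source of material | Patients, informal caregivers, healthcare professionals | Meaning units from patients' experiences |
| Selection or comparison | Patients and caregivers sampled by centre; differences between settings to be understood | Disease etiology and severity |

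**Step 1, topic.** Knowledge needs occur in this one clause only. They are absent from the aim in the Introduction, from the effectiveness outcomes and from the process indicators in Table 1. The nearest remark, in the Discussion, is that caregivers often lack support and information. That concerns caregivers, and it is background rather than an objective.

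**Step 2, participants.** The first reading step covers every transcript. The step that produces the units to be coded names patients only. Table 1, however, lists the experience of caregivers and of healthcare personnel as indicators beside that of patients.

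**Step 3, axes.** Etiology and severity of cirrhosis are attributes of a patient. They could be attached to a caregiver only through the patient cared for, and not to a staff member at all. The clause therefore cannot serve as the comparison for all three groups.

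**Step 4, count.** 4 centres × 5 = 20 patients, and likewise 20 caregivers; 20 + 20 = 40 interviews, or about 10 per centre. The number of staff interviews is not given. Patient and caregiver interviewees are thus spread evenly over centres, yet centre is not among the stated comparisons.

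**The case against.** The strongest reply has four parts.

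1. *Coding is content-driven.* Codes are to reflect what the transcripts contain, and the interviews explore experiences with the intervention, so material on acceptability will be coded. This stands in part. A reader might infer that the coding cannot capture acceptability at all, and the text does not support that. But the next step sorts the codes under knowledge needs, and that is the only topic named that could decide which meaning units count as relevant.

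2. *The word for patient is loose drafting.* The paragraph opens with all transcripts and ends with a check across the whole dataset. This is a fair reading. A reader might conclude that the 20 caregiver interviews (half of the 40) and every staff interview are excluded. That treats one word as an exclusion rule, and no such loss is shown. What remains is that caregivers and staff are never named, and that the comparison axes do not fit them.

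3. *Site differences have other sources.* The process evaluation is mixed-method. Table 1 lists differences between sites under Adoption, where the source shown is information from the sites, and also lists counts of conversations, questionnaires and referrals. This stands: it would be wrong to say that site differences go unexamined because this paragraph omits them.

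4. *The refinement before Phase 3 does not depend on this paragraph alone.* It draws on the mixed-method feasibility findings, and the staff interviews on implementation and impact are placed in Phase 3. This also stands. A reader might infer that the refinement decision is left without any analysis; the documents do not support that.

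It may be added that an article leaves interview guides and coding frames to the full protocol. That would answer a complaint about missing detail. Here the article states a topic, a source and axes, and those conflict with its own endpoints.

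**Conclusion.** The point holds as a mismatch of direction. The stated qualitative analysis is not aimed at the acceptability and appropriateness of the intervention, names one of three interviewed groups, and compares by axes that suit patients only. Its effect is weakened support for these implementation outcomes, not loss of it: inductive coding and the other Table 1 sources can still supply information on acceptability and on sites.

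The primary outcome, the other effectiveness outcomes, the sample size and the economic analyses are unaffected. The correction should be made because a stated aim of the trial is concerned and the change is small.

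The conclusion rests on two assumptions: that the Statistical methods paragraph is meant to govern the interviews described under Implementation outcomes, since no other qualitative analysis is described; and that no separate objective on knowledge needs exists in a document not shown. If one does, the article should declare it in addition, and the analysis for acceptability and appropriateness would still have to be stated.

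**What to change.** Make two changes in the qualitative paragraph under Statistical methods.

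- Where meaning units are identified, replace the reference to each patient with *each participant (patient, informal caregiver or healthcare professional)*.
- Replace the knowledge-needs clause with text such as: *categories will describe the acceptability and appropriateness of the intervention, compared across stakeholder groups and described by study site where the data allow.*

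With about five patients and five caregivers per centre, the account by site should be descriptive, not a formal comparison. Etiology and severity can stay as descriptive axes for patients. The coding can remain inductive; a preset framework is not required. If knowledge needs are of real interest, list them as an additional objective.

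The cost is the rewording of one paragraph and a matching check of the plan for forming categories. No interviews, participants or staff are added.

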## Discussion

The LiverCare study is designed to address the substantial gap in evidence regarding structured, interdisciplinary palliative care for patients with liver cirrhosis. Despite a high symptom burden, high mortality, and marked psychosocial strain, palliative care remains underutilized and poorly integrated in hepatology care pathways [18–20]. Several systemic and cultural factors contribute to this gap, including the unpredictable disease trajectory of cirrhosis, misconceptions equating palliative care with end-of-life care, and limited training among healthcare professionals in addressing the multidimensional needs of this population. By applying a pragmatic, multicenter design, the LiverCare study aims to generate findings with high external validity and real-world relevance, thereby supporting scalable implementation across diverse clinical settings [22].

The intervention explicitly includes informal caregivers, acknowledging the considerable psychological, relational, and practical burden cirrhosis imposes beyond the patient [30–32]. Existing research demonstrates that caregivers experience significant strain and often lack adequate support and information [45]. Enhanced communication and involvement of informal caregivers have been identified as core targets for improving care [45]. By integrating family-centered components and creating structured opportunities for dialogue, the LiverCare study responds to these unmet needs.

A key strength of this study is the hybrid type 1 effectiveness-implementation design, combining evaluation of both clinical and implementation outcomes [21]. Integrating a process evaluation will enable us to distinguish intervention effects from implementation success, explore mechanisms of impact, and assess how contextual factors shape delivery across sites [23]. This is essential in complex intervention research, where positive effects alone do not guarantee sustainable uptake. A failure to recognise the preconditions required to achieve a defined aim may limit generalisability and hinder translation into practice. Implementation science provides the tools to bridge this gap by examining how interventions work in routine systems and identifying what is needed to reach real-world benefit [46].

The inclusion of an initial feasibility study further strengthens the overall study design and reflects the MRC framework’s recommendation to assess feasibility before conducting a full evaluation of complex interventions [23]. Feasibility testing allows us to assess acceptability, fidelity, recruitment pathways, workflow, and data-collection procedures before launching the full trial [47]. These insights will guide refinements of both the intervention and implementation strategy, thereby reducing the risk of attrition, non-adherence, and site-level variation later in the study. Taken together, the feasibility phase and process evaluation increase the likelihood that the intervention will be not only effective but also implementable and scalable.

The multicenter design enhances generalisability but introduces the possibility of variability in prerequisites between sites in terms of culture, staffing, resources, and local workflows. Such heterogeneity may affect fidelity and complicate interpretation of outcome data [23]. The process evaluation is therefore crucial in documenting contextual influences and enabling nuanced understanding of how and why outcomes differ across settings. This knowledge is essential for future scale-up beyond the study sites.

The results of the LiverCare study will be disseminated in peer-reviewed journals and at national and international conferences. Findings will inform clinical practice and support education and competence development for healthcare professionals working with advanced liver disease. Insights will also guide future implementation strategies and contribute to strengthening palliative care provision within hepatology.

## Data Availability

Upon completion of the study, anonymised data will be stored securely in accordance with national data protection regulations. Access to the final dataset may be granted upon reasonable request to the corresponding author, subject to relevant ethical approvals and data protection requirements.

## Abbreviations

ACP: Advance Care Planning
ARLD: Alcohol-related liver disease
CBI: Copenhagen Burnout Inventory
EQ-5D-5L: EuroQol five-dimension five-level questionnaire
HRQoL: Health-related quality of life
MELD: Model for End-Stage Liver Disease
MRC: Medical Research Council
PRO-Pall: Patient-Reported Outcomes in Palliative Care questionnaire
QALY: Quality-Adjusted Life Year
RE-AIM: Reach, Effectiveness, Adoption, Implementation, and Maintenance framework
SPICT: Supportive and Palliative Care Indicators Tool
ZBI: Zarit Burden Interview
